**PFS**

PFS is defined as the time from randomization to the first time of disease progression or death from any cause, whichever occurs first. If the subject did not experience disease progression or death, then PFS was defined as the date of the last confirmed progression-free. Patients who discontinued for reasons other than disease progression (no subsequent tumor image) and starting the therapy after the trial were censored at the time of discontinuation or initiation of treatment. In cases other than those described above, pre-planned sensitivity analyses will undertake to define PFS based only on the date of confirming tumor progression events. New onset other tumor is not considered indicative of PD and is not censored as data.

If the image examination and evaluation show progression, the data of disease progression is not the time showing signs of disease progression, but the time of the development of radiologically noticeable PD.

- - 1. **The secondary endpoints**

**OS**

OS is defined as the time from the randomization data to the date of death due to any cause. OS is censored at the date of the last visit for those still alive at the time of the last visit. Patients lost to follow-up were censored at the time of the last contact. Censored OS is defined as the time from randomization to censor.

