**TTPD**

TTPD is defined as the time from the date of enrollment to the first date of documented progression according to RECIST v1.1.

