The SS population will serve as the population for the safety analysis. All randomized subjects have received at least one dose of the research drug and have a post-administration safety record.

- - 1. **Statistical analysis plans**

All statistical analysis will be performed using the SAS statistical package (≥9.3 version) with a two-sided test. P ≤0.05 is considered significant, with 95% confidence intervals (CI).

1. Baseline

Quantitative data including age, height, weight, and so on are described as mean ± standard deviation (SD), median, maximum, and minimum values, and qualitative data such as gender and ECOG score are reported by number and frequency.

1. Efficacy assessment

The primary endpoint of this trial, PFS, will be estimated using the Kaplan-Meier method with a 95% CI and presented with the Kaplan-Meier curve. The comparison of PFS between intervention arms will be performed using a stratified log-rank test. The HR and the corresponding 95% CI will also be provided based on a Cox proportional hazard model, using such as age, ECOG PS, and EGFR mutations (exon 19 deletions or an exon 21 mutation) as stratification factors.

The secondary endpoint such as OS, TTPD, and DoR will be analyzed in the same method as the primary endpoint. The cochran-mantel-haenszel (CMH) method or Chi-square test will be used to compare ORR and DCR between the groups, and Fisher's exact test method will be used to calculate ORR, DCR, and 95% CI. The Student t-test or Wilcoxon rank sum test will be used to compare the QoL between the groups.

1. Safety analysis

Safety analysis will be mainly descriptively summarized and the mean or incidence of pre- and post-administration examination tests (if necessary). Vital signs, physical examination, and laboratory tests will be demonstrated mainly through the changes from baseline in clinical and the incidence of abnormalities. All AEs will be coded using the Medical Dictionary for Regulatory Affairs (MedDRA) for safety analysis. Summary and compare the incidence of all AEs, treatment-emergent adverse events (TEAEs) with grade 3 or more, serious TEAEs, and so on between two intervention arms will be tabulated according to MedDRA PT and primary system organ class (SOC), as well as CTCAE grading.

- 1. **Interim analysis**

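### The PFS sensitivity analysis described in the protocol, read literally, leaves out deaths, nearly duplicates TTPD and does not vary the censoring rule

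*Protocol*

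**What the plan says.** Protocol section 10.1 (Primary endpoint, PFS) gives the primary definition: "PFS is defined as the time from randomization to the first time of disease progression or death from any cause, whichever occurs first". It then sets a censoring rule: "Patients who discontinued for reasons other than disease progression (no subsequent tumor image) and starting the therapy after the trial were censored", with the censoring date being discontinuation or the start of the new treatment. The next sentence opens with "In cases other than those described above" and continues that "pre-planned sensitivity analyses will undertake to define PFS based only on the date of confirming tumor progression events". The protocol describes no other form of PFS sensitivity analysis. The sentence does not say which cases it covers or what happens to deaths without documented progression.

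Among the secondary endpoints in the same section, "TTPD is defined as the time from the date of enrollment to the first date of documented progression according to RECIST v1.1". Section 13.2 adds: "The secondary endpoint such as OS, TTPD, and DoR will be analyzed in the same method as the primary endpoint".

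**The concern.** A sensitivity analysis of a primary endpoint normally keeps the question fixed and varies an assumption that could be wrong. Here the wording appears to do the reverse. It changes the event, by restricting it to progression, and keeps the assumption most open to doubt.

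That assumption is the censoring. Patients who stop for toxicity and have no later scan, or who move to another therapy, may differ in prognosis from those who stay on treatment. An add-on drug with its own toxicity may also produce more of them in one arm than in the other. If so, the censoring is informative and the PFS comparison could be biased. The analysis described would carry the same possible bias.

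The component that seems to be removed is also the one in which fatal toxicity counts against anlotinib. Section 7.4 anticipates bleeding, thrombosis and gastrointestinal perforation. A progression-only analysis does not respond to deaths from such causes.

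**Working it through.** **1. The plan's own figures.** Section 3.3 assumes median PFS of 15 against 10 months, so HR = 10/15 = 0.667 under exponential times, with two-sided α = 0.05 and 80% power.
- Schoenfeld events: 4 × (1.960 + 0.842)² / (ln 1.5)² ≈ 191, against 192 stated. Power at 192 events is 80.2%.
- With uniform accrual over 18 months, 18 months of follow-up and 124 per arm, the event probabilities are 0.7045 and 0.8359. Expected events are 87.4 + 103.7 = 191.0 (stated: 88 + 104 = 192).
- Dropout: 248 / 0.8 = 310.

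The sample size reproduces, so the point concerns a definition and not a figure.

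**2. The definitions side by side.**

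| | PFS | Sensitivity analysis, read literally | TTPD |
|---|---|---|---|
| Event | progression or any death | progression only | progression only |
| Time origin | randomization | randomization (as PFS) | enrollment |
| Method | Kaplan-Meier, log-rank, Cox | not stated separately | as for PFS |
| Censoring at discontinuation or new therapy | yes | not varied | no rule of its own stated |

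The only written difference in definition between the second and third columns is the time origin.

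**3. What removing deaths does.** The protocol gives no share of PFS events that are deaths without progression, so the share *s* among control-arm events is assumed, as is the death HR. With constant hazards, and non-progression deaths treated as censoring in the progression-only analysis:

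PFS HR = (1 − s) × 0.667 + s × (death HR), and progression-only HR = 0.667.

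Example, s = 10% and death HR 2.0: 0.90 × 0.667 + 0.10 × 2.0 = 0.60 + 0.20 = 0.80.

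| s | Death HR 1.0 | Death HR 1.5 | Death HR 2.0 | Progression-only HR |
|---|---|---|---|---|
| 5% | 0.683 | 0.708 | 0.733 | 0.667 |
| 10% | 0.700 | 0.750 | 0.800 | 0.667 |
| 15% | 0.717 | 0.792 | 0.867 | 0.667 |

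The PFS HR moves and the progression-only HR does not. In the mildest cell (5% deaths, equal death hazards) the gap is 0.683 against 0.667, which is negligible.

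**4. Events lost.** If 5%, 10% or 20% of the 192 PFS events were deaths without progression, a progression-only analysis would keep about 182, 173 or 154 events. Schoenfeld power at HR 0.667 would be 78.2%, 76.0% or 71.0%. This loss of information is secondary to the change of question.

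**The case against.** The strongest objection is the opening qualifier, "In cases other than those described above". Death has already been described as a PFS event earlier in the same paragraph. On that view the sentence is only a dating rule for residual cases, using the date on which progression was confirmed, and deaths still count. The section's closing paragraph, which dates progression by the radiological finding, has a similar concern. This reading is possible and cannot be excluded. However, progression, death, absence of an event, discontinuation and new therapy are all covered beforehand, so the residual cases are undefined. The sentence needs rewording on either reading.

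A reader might infer more than the text supports:
- **That this is the trial's only PFS sensitivity analysis.** It is the only form described in the protocol. The text uses the plural, and a statistical analysis plan, not at hand, may add others.
- **That it cannot test the PFS result at all.** Set beside PFS, a progression-only analysis shows whether the result depends on counting deaths. A visible gap between the two would itself point to them.
- **That it would be taken as confirmation of a failed or weakened primary result.** Section 3.2 rests superiority on PFS. Excess deaths would also appear in OS, in serious adverse event reporting and in the data monitoring committee's review.
- **That anlotinib will cause excess non-progression deaths.** Nothing in the protocol quantifies this, and the death HRs above are illustrations.

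What stands is narrower: the sentence is unclear about scope and about deaths, and on its ordinary meaning it varies the event and not the censoring.

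**Conclusion.** The point holds as a defect in how a supportive analysis is fixed. Read literally, the sentence changes the estimand, nearly duplicates TTPD, and leaves unexamined the censoring at discontinuation without later imaging or at the start of new therapy.

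Its numerical size depends on inputs that the protocol does not give. At the planned effect, taken as the progression HR, with 10% of control-arm events being deaths, death HRs of 1.0, 1.5 and 2.0 give PFS HRs of 0.70, 0.75 and 0.80 against an unchanged 0.667. These values assume constant hazards. The effect of the untested censoring cannot be sized from the document.

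The primary definition, the sample size and the primary test are not affected. The change is worth considering because it is cheap; it is not a condition for a valid primary result.

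**What to change.** Replace the sentence in section 10.1 with one to this effect: *The pre-planned sensitivity analysis of PFS keeps progression or death from any cause as the event and counts every documented event, regardless of treatment discontinuation or the start of new anticancer therapy.* Remove the opening qualifier, and leave progression-only analysis to TTPD.

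The cost is one sentence and no new data collection. Section 9.3 already continues tumour evaluation every 2 cycles after discontinuation without radiological progression. Section 9.5 already records date and cause of death, with contact at least every 3 months.

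The limitation should be stated with the analysis. Evaluation under section 9.3 ends when another cancer therapy begins, and later follow-up is by telephone. After a switch the analysis therefore captures mainly deaths and only part of the progressions. It tests the censoring rule but does not fully replace the missing scans.

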**ORR**

The proportion of patients with confirmed tumor volume reduction to pre-specified values and maintenance of minimum time requirements, including the number of subjects with an objective response (PR or CR). Objective responses are assessed per RECIST v1.1. Participants must have at least one measurable lesion at baseline, and the efficacy criteria were classified as CR, PR, SD, and PD according to RECIST v1.1.

**DCR**

The percentage of subjects with the disease control (PR, CR, or SD [≥ 8 weeks]) will be presented.

**DOR**

The time from first documented CR or PR to disease progression or death from any cause, whichever occurred first (taking as reference for PD the smallest measurements recorded in the trial).

**TTPD**

TTPD is defined as the time from the date of enrollment to the first date of documented progression according to RECIST v1.1.

**QoL**

The changes in relevant clinical symptoms and objective examination results of patients before and after treatment were observed for scoring, and the scoring results of each domain of the scale were recorded in the eCRF according to the requirements of the quality of life scores. QoL is assessed by the EORTC QLQ-C30 (version 3) and EQ-5D.

- 1. **Safety analysis**
     1. **AEs**
        1. **Definitions of AEs**

AE is defined as any untoward medical occurrence in a patient or clinical investigation subject administered a pharmaceutical product and which does not necessarily have to have a causal relationship with this treatment. Any AEs that occur within 30 days from the initiation of the study drug to the end of treatment in this trial, regardless of whether or not have a causal relationship with this treatment, will be determined as AEs.

Investigators are required to record any AEs in subjects, including the events, AEs-related symptoms, time of occurrence, severity, duration, management, and outcomes.

- - - 1. **AEs grade**

The severity grade of any AEs will be assessed according to the definitions in NCI-CTCAE v4.0. For AEs that are not listed in the table, the following criteria can be referenced.

Grade I is defined as mild; asymptomatic or mild symptoms; clinical or diagnostic observations only; intervention not indicated.

Grade II is defined as moderate; minimal, local, or noninvasive intervention indicated; limiting age-appropriate instrumental activities of daily living (ADL, instrumental ADL refers to preparing meals, shopping for groceries or clothes, using the telephone, managing money, etc).

Grade III is defined as severe or medically significant but not immediately life-threatening; hospitalization or prolongation of hospitalization indicated; disabling; limiting self-care ADL (self-care ADL refers to bathing, dressing and undressing, feeding self, using the toilet, taking medications, and not bedridden).

Grade IV is defined as life-threatening consequences; urgent intervention is indicated.

Grade V is defined as death related to AE.

**Note:** For abnormal AEs or abnormal laboratory test indicators allowed by the inclusion criteria at the time of enrollment, the severity of the AEs and drug adjustments were performed according to the investigator’s discretion.

- - - 1. **Causality to study drugs**

An AE is any unintended medical occurrence in a clinical study after the signing of informed consent, which does not necessarily have a causal relationship with the treatment, regardless of whether it is assigned to the experimental groups or even the administration of drugs. Any abnormal changes in objective laboratory tests should be recorded faithfully, together with the time of occurrence, severity, duration, management, and outcomes. Relationships between the study drug and AEs were rated by the investigator as definitely, probably, possibly, unlikely, and unrelated according to five criteria. Definitely, probably, and possibly are classified as drug-related AEs and the incidence of AEs is calculated using the above three as the numerator and the total number of subjects in the safety assessment set as the denominator. The criteria of causality assessment are as follows.

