| Study Procedures | Group A (experimental group): 250 mg gefitinib, po, qd + 12 mg anlotinib hydrochloride capsule, po, qd, D1-D14; administered under fasting conditions (administration of the two drugs at the same time every day), every 3 weeks;  Group B (control group): 250 mg gefitinib, po, qd + anlotinib hydrochloride placebo, 1 tablet, po, qd, D1-D14; administration of the two drugs at the same time every day taking medication at the same time every day), every 3 weeks.  Drugs will be administered every 21 days until disease progression, intolerable toxicity, withdrawal of consent, or drug discontinuation according to the investigator's judgment. |
| Endpoints | Efficacy is evaluated every 2 cycles (6 weeks) after enrollment and every 3 cycles (9 weeks, 63±7 days) from 27 cycles using RECIST 1.1 criteria;  **Primary Endpoints:**  Progression-free survival (PFS)  **Secondary Endpoints:**  1. Overall Survival (OS)  2. Overall Response Rate (ORR)  3. Disease control rate (DCR)  4. Time to disease progression (TTPD)  5. Duration of Response (DoR)  6. Quality of life score (QoL) |
| Safety | Any adverse events (AEs) that occurred in all subjects during the clinical study period will be observed, including abnormal clinical symptoms and vital signs, and abnormalities in laboratory tests. The clinical characteristics, severity, time of occurrence, duration, treatment methods, and prognosis of adverse events will be recorded; meanwhile, the correlation between adverse events and the study drugs will be determined. The safety of drugs is evaluated according to National Cancer Institute's Common Terminology Criteria for Adverse Events (NCI-CTC AE) version 4.0. |
| Exploratory Study | The mechanism of drug resistance will be monitored by next-generation sequencing (NGS) before treatment, at the first efficacy evaluation, and during tumor progression. |

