| Statistical Analysis | **Efficacy analysis**  For the PFS (primary endpoint), the median value and 95% confidence interval (CI) are estimated and survival curves are obtained using the Kaplan-Meier method. Survival differences between the two groups are estimated by log-rank tests. COX regression analysis is used to compare the survival between the two groups after adjusting for stratification factors such as EGFR mutation site, gender, PS score, and pathological type; the hazard ratio (HR) and 95% CI after adjusting for the above stratification factors are calculated.  For the secondary endpoints, such as OS, TTPD, and DoR, the median value and 95% CI are estimated and survival curves are obtained using the Kaplan-Meier method. The log-rank test is used to compare the survival between the two groups; DCR and ORR with 95% CI are calculated, and comparisons between treatment groups are performed using a Cochran-Mantel-Haenszel (CMH) test or chi-square test. Two independent samples will be compared for the differences between the two groups in QoL scores by the t-test or Wilcoxon rank sum test.  **Safety** **analysis**  Descriptive statistical analysis is mainly used, and the mean or incidence of examination results before and after administration could be compared if necessary. Vital signs, physical examination, and laboratory tests mainly describe the changes before and after treatment and the relationship between abnormal changes and study drugs. All AEs are standardized by MedDRA code, and the incidences of AEs and grade 3 or above AEs are summarized and compared between the two groups according to system organ class (SOC) and preferred language (PT) in MedDRA code and CTCAE classification. The AEs and serious AEs occurred in this study are also summarized in the table. |
| Prespecified Efficacy Analysis | An Independent Data Monitoring Committee (IDMC) will be established to conduct 1-2 interim analyses to provide further recommendations and to ensure the safety of subjects.  Final analysis: It is performed when approximately 192 PFS events have occurred |
| Study Schedule | Enrollment date of the first subject: January 2019  Enrollment date of the last subject estimated: June 2021  Estimated date of the end of the study: December 2022 |

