2. platelets (PLT) ≥100×10^9^/L;
3. hemoglobin (Hb) ≥100g/L;

- **Biochemistry:**

1. total bilirubin (TBIL) <1.5×ULN；
2. alanine aminotransferase (ALT) and aspartate aminotransferase (AST) <2.5×ULN; ALT and AST <5×ULN in patients with liver metastases;
3. blood Urea Nitrogen (BUN) and creatinine (Cr) ≤1×ULN or creatinine clearance rate ≥50ml/min (Cockcroft-Gault formula);
4. Women of reproductive age must have already used effective contraception or have negative serum or urine pregnancy test results within 7 days before enrollment and be willing to use an adequate method of contraception during the trial period and 8 weeks after the last drug administration. For men, consent is given to use an appropriate method of contraception or to have been surgically sterilized during the trial period and 8 weeks after the last drug administration;
5. Be willing and able to provide written informed consent for the trial, and comply with all aspects of the protocol.
   1. **Exclusion criteria**

Subjects who meet any of the following criteria are not eligible to enter the study:

1. Small cell lung cancer (including mixed small cell and NSCLC);
2. Symptomatic brain metastases (patients with stable brain metastases who have completed treatment 21 days before enrollment are eligible, but have no symptoms of cerebral hemorrhage confirmed by brain MRI, CT, or venography);
3. Tumor lesion of ≤5 mm from the large blood vessels, or central tumor invading the local large blood vessels, or significant pulmonary cavitary or necrotic tumors by imaging (computed tomography [CT]/ magnetic resonance imaging [MRI]);
4. Patients with hypertension who are being treated with a combination of two or more antihypertensive drugs;
5. Patients with positive T790M mutations from genetic test;
6. Cardiovascular diseases: class II or more of myocardial ischemia or myocardial infarction, arrhythmia due to poorly controlled (including men with corrected QT interval [QTc] ≥450 ms and women with QTc ≥470 ms); patients in New York Heart Association (NYHA) class III-IV cardiac dysfunction, or left ventricular ejection fraction (LVEF) <50% by echocardiography;
7. Patients with a history of interstitial lung disease or concurrent interstitial lung disease;
8. Abnormal coagulation function (INR >1.5 or prothrombin time [PT] >ULN+4 seconds or APTT >1.5 ULN) with a bleeding tendency, or are receiving thrombolytic or anticoagulant therapy;
9. Hemoptysis (2 teaspoons or more per day) before enrollment;

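### The Note in Protocol section 10.2 leaves AE severity to investigator discretion for abnormalities allowed at entry, although AEs are otherwise graded, compared and tabulated by CTCAE v4.0

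*Protocol*

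**What the plan says.** The general rule in Protocol section 10.2, AEs grade, has no exception: "The severity grade of any AEs will be assessed according to the definitions in NCI-CTCAE v4.0". For events that CTCAE does not list, the same subsection supplies a generic Grade I to V scale.

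A Note closes the subsection. It deals with AEs and laboratory findings that were "allowed by the inclusion criteria at the time of enrollment, the severity of the AEs and drug adjustments were performed according to the"; the standard it then names is the discretion of the investigator. It names no scale and no point at which CTCAE grading takes over again.

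The reporting text carries no matching exception:

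- The Safety row of the synopsis evaluates safety by "Common Terminology Criteria for Adverse Events (NCI-CTC AE) version 4.0".
- The Statistical Analysis row of the synopsis says that "the incidences of AEs and grade 3 or above AEs are summarized and compared between the two groups", by system organ class, preferred term and CTCAE class.
- Section 13.2, Safety analysis, says that AE incidences "will be tabulated according to MedDRA PT and primary system organ class (SOC), as well as CTCAE grading".

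Section 5.2 sets the entry limits that define the Note's scope. Among them are "ALT and AST <5×ULN in patients with liver metastases" and, for BUN and creatinine above the ULN, the alternative "or creatinine clearance rate ≥50ml/min (Cockcroft-Gault formula").

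**The concern.** Section 10.2 gives two rules for the same quantity. An investigator who sees a raised ALT in a patient admitted with a raised ALT can follow the general rule and assign the CTCAE grade, or follow the Note and assign a severity by judgement. The eCRF entry would look the same either way, and the tables would label both as CTCAE grades.

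At stake is how the safety tables can be read. A CTCAE grade for a laboratory term is meant to be reproducible from the value and the laboratory's limits. A severity assigned by judgement is not, and it may differ between sites and between patients with the same value. Severity is fixed at the site when the event is recorded. A later analysis plan can define treatment emergence or baseline-grade handling, but it cannot turn a discretionary severity into a CTCAE grade unless the values are regraded.

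**Working it through.** The protocol states no figure on this point, so the check compares the texts.

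**1. Which rule governs.** The general rule covers any AE. The Note removes a subset from it for severity as well as for drug adjustment. No other section narrows the Note. The dose criteria in section 7.2 are tied to NCI grades, and the grading tables in section 7.4 cover hypertension, hand-foot skin reaction and proteinuria. Neither says how to grade a liver or renal value that was abnormal at entry.

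**2. Which abnormalities are covered.** Section 5.2 names eight laboratory parameters.

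| Parameter | Entry limit | Abnormal value shown to be allowed? |
| --- | --- | --- |
| Total bilirubin | <1.5×ULN | Yes, above the ULN |
| ALT, AST | <2.5×ULN; <5×ULN with liver metastases | Yes, above the ULN |
| BUN, creatinine | ≤1×ULN, or clearance ≥50 ml/min | Yes, through the clearance alternative |
| ANC, platelets, haemoglobin | ≥1.5×10^9/L, ≥100×10^9/L, ≥100 g/L | Depends on laboratory lower limits, which are not given |

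Five of the eight (bilirubin, ALT, AST, BUN, creatinine) are therefore shown to be covered. The other three are undetermined.

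**3. Whether the subset matters for this drug.** Table 3 (12 mg anlotinib, 21 patients, whole study, grade I/II) lists raised ALT in 10 (47.62%), raised AST in 9 (42.86%) and raised total bilirubin in 8 (38.10%). This does not size the effect here. It shows only that on-treatment change in the covered parameters is foreseeable.

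**4. Where discretion ends.** Two readings are possible. Take, as an illustration, a patient with liver metastases admitted with ALT at 4×ULN.

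- *Reading A:* discretion stops at the entry limit. Severity is discretionary below 5×ULN, and CTCAE applies from there. An effect on the grade 3 or above tables would then need a value inside the limits to be grade 3. The protocol does not print the CTCAE cut-offs for these tests, so no such effect is shown.
- *Reading B:* discretion follows the abnormality. However far ALT rises, its severity stays discretionary, and a grade 3 or above event could be recorded with another severity.

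The Note does not choose between them. AE severity and drug adjustment are both on-treatment matters, so Reading B cannot be excluded.

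**5. Size.** A number would need the share of patients entering with an allowed abnormality, how often it worsens, and how often the discretionary severity departs from the CTCAE grade. The protocol gives none of these. The effect is zero if investigators use CTCAE grades under the Note anyway. No upper end can be derived.

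**6. Whether it can be repaired from collected data.** Sections 9.1 and 9.2 list bilirubin, ALT, AST, creatinine and urea (the measure of BUN) at screening and at treatment visits, and the blood counts as well. All eight parameters can be regraded from recorded values.

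**7. Timing.** Version 1.6 is dated October 29, 2021. The synopsis estimates last enrollment in June 2021, about four months earlier, and study end in December 2022, about fourteen months later. New wording would reach later events only.

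**The case against.** The strongest reply is that the Note contains its own boundary. It speaks of abnormalities the inclusion criteria allow, and a value past the entry limit is no longer allowed, so the general rule resumes. The Note also introduces no rival scale, sits directly under the CTCAE rule, and is awkwardly translated. It may have been meant only to account for baseline grade. In addition, section 13.2 summarises laboratory data separately, since "laboratory tests will be demonstrated mainly through the changes from baseline in clinical and the incidence of abnormalities", and that summary does not depend on the AE grade. Baseline-grade rules commonly belong in the SAP, and a synopsis need not repeat a note.

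Much of this stands. The boundary reading is reasonable, and on that reading no effect on the grade 3 or above tables is shown. The separate laboratory summaries partly offset the problem. The rule for treatment emergence relative to baseline can stay in the SAP.

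It does not remove the conflict. Even inside the entry limits, the Note replaces CTCAE grading of severity with judgement, while the tables claim CTCAE grades. The benign intention may be right, but the text does not state it.

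A reader might go further and infer that grade 3 or above toxicity is understated, or understated on anlotinib in particular. The documents do not support that. The Note gives discretion no direction, it applies to both arms alike under the blinding in section 4.2, and reaching grade 3 or above depends on Reading B. Nor do they support treating all eight entry parameters as covered: for the three blood counts the protocol does not show that any abnormal value is admitted.

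**Conclusion.** The point holds as a minor inconsistency in how AE severity is fixed. Section 10.2 sets CTCAE v4.0 for every AE and then leaves severity to judgement for abnormalities allowed at entry, while the synopsis and section 13.2 report CTCAE grades without exception. For bilirubin, ALT, AST, BUN and creatinine abnormal at entry, the recorded severity may not be a CTCAE grade.

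The effect cannot be sized from the protocol and may be nil in practice. It extends to the grade 3 or above comparison only if investigators used discretion for worsening beyond the entry limits. No direction between arms is implied, and no efficacy endpoint depends on AE grade. The conclusion rests on the wording of the Note as it stands and on the absence of any other section that limits it.

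**What to change.** Replace the Note with a sentence that removes severity from it:

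*All AEs, including worsening of abnormalities present at entry, are graded by NCI-CTCAE v4.0; for abnormalities allowed at entry, drug adjustment is at the investigator's discretion.*

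New wording does not change severities already entered. For the affected laboratory AEs already recorded, derive the CTCAE grade from the values collected at screening and treatment visits, using the laboratory limits against which eligibility was judged. Do this before unblinding; the documents do not say whether unblinding has occurred, and if it has, apply the same fixed rule to every record without reference to treatment.

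The cost is one sentence and a small amount of regrading. No new laboratory data are needed for scheduled visits. Values from unplanned visits (section 9.6), and any non-laboratory AE whose severity was set under the Note, would need a check against source records.
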